## Design and methods

### Study design

POPS is a longitudinal, prospective cohort study that will be conducted with practitioners and their patients undergoing potentially painful dental procedures. Data about baseline pain intensity and patient demographics will be collected prior to the procedure. The patients will receive push notifications through text messages via the FollowApp.Care platform on their mobile devices which asks them to comprehensively record their pain experience at designated time intervals on days 1, 3, 5, 7, 14, and 21 following their procedure. At the end of the 1st week (day 7), they will be asked to report their satisfaction with their post-operative pain management. On Day 23, after the procedure, they will be requested to complete a questionnaire to measure the platform’s usefulness and ease of use. All participating practitioners will be invited to complete a questionnaire to assess the platform’s perceived usefulness and ease of use. A subgroup of practitioners will also be invited to participate in debriefing/interviews to qualitatively evaluate their experiences with using FollowApp.Care for managing their patients’ post-op pain.

### Study sites

The study is being executed in the National Dental PBRN, a collective network of dental practices that includes private and group practices, public health clinics, community health centers and Federal Qualified Health Centers (FQHCs), academic institutional settings, and special patient population [32]. Since its inception in 2005, the Network has matured into a national network with coverage in urban and rural areas and participation by general dentists, dental specialists, and dental hygienists [33]. The Network is interested in increasing the study and use of HIT to collect PROs within its clinics. It is highly productive, with 19,827 practitioners participating in one or more Network studies [33], and 762 practitioners actively being part of at least one clinical study [34, 35]. The Network has been involved in 58 studies. Practice-based research promotes not only the collection of data at the provider and patient levels but also allows the gathering of patient perspectives before, during, or after the visit. The Network’s infrastructure has matured through various management initiatives into a nimble yet continuous, quality-improvement conscientious network [36]. It is rapidly moving toward achieving the vision of a Learning Health System [37]. Hence, this environment is ideal for developing a practical, focused post-operative pain management study. The six Network geographic regions in the US will be informed of the study protocol and opportunity to participate. We anticipate that all Network practitioners stratified by state, urban/rural, and practice size, will be eligible to participate; between 150 to 215 Network practitioners will be recruited.

### Study population and eligibility criteria

The study participants include Network dental practitioners who perform endodontic, periodontal, oral surgery, and/or implant dental surgical procedures and their patients. Eligibility criteria for practitioners include: 1) Be a Network practitioner deemed as study ready, 2) Be a dentist who performs at least one of the identified Code on Dental Procedures and Nomenclature (CDT Code) [38] procedures per week (Endo CDT codes D3000-D3999, Perio CDT codes D4200-D4299 and D4341 and D4342, Oral Surgery CDT codes D7000-D7999 excluding D7287, D7288, D7880, D7881, D7899, D7921, 12 CDT codes from Implant Services (D6000-D6199): D6010, D6011, D6012, D6013, D6040, D6050, D6100, D6101, D6102, D6103, D6104, D6081) and has access and willingness to use the platform through an internet browser using a smartphone, tablet, computer, or laptop for patient care purposes. Eligibility criteria for patients include: 1) Are willing and able to comply with all study procedures; 2) Planning to undergo one or more of the aforementioned surgical procedures; 3) Have access to and willingness to use their smartphone for study purposes, and 4) Have not already participated in the study previously. Each participating practitioner will be asked to recruit a minimum target of approximately three consenting patients per month, although recruitment targets will be further refined once the number of enrolled practitioners is clear. Practitioners may enroll patients at a rate and consecutive process (i.e., 1 day per week, 1 week per month, etc.) that best suits their practice situation.

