In our pilot study (AHRQ 1U18HS026135), we successfully explored how an innovative mobile health intervention (FollowApp.Care®) could optimize the quality of acute post-op dental pain management by collecting PRO data from patients after dental procedures. However, it also taught us a number of implementation barriers. Some of these barriers are not new to those collecting PRO data, including difficulties with optimizing workflows and minimizing logistical burdens, further exacerbated by the expanded precautionary settings during COVID; data management in light of staff turnover; and staff training and providers [30, 31]. Barriers specific to implementing dental PROs using mHealth included making sure that providers see and act upon alerts timely; a hybrid approach to recruitment of patients due to the COVID environment; inaccurate phone numbers, and phone carrier contractual issues that prevented text messaging.

These barriers can substantially hamper the implementation of PROs by the general dentist, to the detriment of advancing patient-centered care in the dental arena. In the POPS (**P**ost-**O**perative **P**ain **S**tudy) trial (UH3DE029158, Understanding Pain after Dental Procedures), we seek to address the gap in knowledge by implementing an existing mHealth technology (FollowApp.Care) in the dental office setting. Through the FollowApp.Care platform, we will actively track pain and other complications following dental procedures. We expect to identify specific pain experiences associated with surgical dental procedures promptly and precisely. We will also collect information about pain management strategies and medications recommended by the practitioner and utilized by the patient. The results of this study will provide insight into pain and other postoperative complications experienced by patients through approximately 3 weeks following common dental procedures. We will also be able to gauge to what extent practitioners are interested in adopting mHealth technology. We will also learn how patients like to be engaged with text messaging to report post-operative pain and complications.

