### Secondary objectives are

Assess post-operative pain management strategies at 1 week following dental surgical procedures, as recommended by practitioners, and reported by patients.Evaluate practitioner and patient acceptance of FollowApp.Care. We will evaluate FollowApp.Care usage, perceived usefulness, ease of use, and impact on clinical workload.

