## Hypotheses

The study includes the following hypotheses:

### Hypothesis 1

There is a significant difference in pain intensity measured over time and the dental procedure groupings after adjusting for pain management strategies and other complications. More specifically, are their significant variations in pain intensity due to different treatments after adjusting for:pain management strategy (e.g., pain medications used, adherence to pain management strategy, the usage of non-medicine methods for pain)other complications

### Hypothesis 2

There is a significant difference in pain interference measured over time and the dental procedure groupings, after adjusting for pain management strategies and other complications. More specifically, are their significant variations in pain interference due to different treatments after adjusting for:pain management strategy (e.g., pain medications used, adherence to pain management strategy, the usage of non-medicine methods for pain)other complications

### Hypothesis 3

There is a significant difference in patient satisfaction measured at the end of the 7-day period and dental procedure groupings, after adjusting for pain management strategies and other complications. More specifically, are their significant variations in patient satisfaction due to different treatments after adjusting for:pain management strategy (e.g., pain medications used, adherence to pain management strategy, the usage of non-medicine methods for pain)other complications.

### Hypothesis 4

Reported technology acceptance metrics; performance expectancy (PE), effort expectancy (EE), social influence (SI), and behavioral intention (BI) will be consistent with high acceptance of the FollowApp.Care platform.

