UTAUT Questionnaire	After practitioner completes enrollment of all their patients	Explores four core constructs: performance expectancy, effort expectancy, social influence, and facilitating conditions as direct determinants of behavioral intention and behavior	Practitioners
electronic Case Report Form (eCRF)	Days 0 and 21	Two eCRFs: - Practitioner info (practitioner characteristics) - Patient info (diagnoses and procedures, pain levels, pain management plan, and complications)	Practitioners
Debriefing/interview	After practitioner completes enrollment of all their patients	Practitioners’ experiences with using FollowApp.Care for managing their patients’ post-op pain.	Practitioners

Patients will also be asked to evaluate the usability of the FollowApp.Care system by completing the 10-item, System Usability Scale survey and providers the UTAUT questionnaire. Once the patient component of the study has been concluded, we will conduct telephone interviews with providers to qualitatively evaluate their experiences with using FollowApp.Care for managing their patients’ post-operative pain, including its impact on their clinic workload, workflow patterns, and satisfaction with the effectiveness of pain management.

See Table 3 for an overview of study activities.

**Table 3 Tab3:** Study activities

Task	Description of implementation/operationalization
1. Network Site Selection	We anticipate that all Network practitioners stratified by state, urban/rural, and practice size, will be eligible to participate. We will work with the Network coordinators to assure all sites are informed of the study protocol and the opportunity to participate.
2. Practitioner Recruitment and training	The Network site coordinators will use established protocols to recruit practitioners. The study team will work with the coordinators and the Network Communications Director to assure the dissemination of the study opportunity. The study team will provide the coordinators with all online training materials. Coordinators may decide to add an in-person training component. Study personnel will be available remotely via video conference/phone calls to support all training efforts.

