3. Patient screening and enrollment	Each participating office will decide if practitioners or office staff will screen/enroll patients in the study. The office staff who enroll patients will need to have successfully completed appropriate training. Each participating office will maintain a log of screened and enrolled subjects. On a weekly basis, office staff will record their summary screening/enrollment information in the electronic data capture (EDC) system. Practitioners will enroll patients via a consecutive process that best suits their practice situation, i.e., they will approach any patient who may meet the inclusion criteria during the days and/or times when the office is participating in research activities.
4. FollowApp.Care platform activation	Enrolled practitioners will individually be able to request their FollowApp.Care notification preferences, for example, they can choose to receive notifications by email or text. Notifications will be sent to practitioners based on predefined thresholds defined in the manual of procedures (MOP).
5. Patient evaluation (Usability questionnaire)	Patients will complete a Usability survey (SUS) on day 23 using the FollowApp.Care platform.
6. Practitioner evaluation (debriefing/interview session and UTAUT questionnaire)	Once the patient component of the study has been concluded, we will administer the UTAUT Questionnaire to all participating practitioners to assess their perceived usefulness and perceived ease of use of FollowApp.Care as predictors of their usage behavior. Thereafter, we will conduct virtual debriefing/interviews with up to 45 purposefully selected practitioners to qualitatively evaluate their experiences with using FollowApp.Care for managing their patients’ post-op pain. These debriefing/interview discussions will be audiotaped and transcribed for analysis.

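### Only dentists willing to use FollowApp.Care can enrol, so the study measures acceptance among willing users and cannot gauge how far practitioners in general are interested in adopting it

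*Protocol article*

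**What the plan says.** **Entry.** Under Study population and eligibility criteria, a practitioner must be in the Network and study ready, be a dentist who performs at least one listed procedure a week, and be someone who "has access and willingness to use the platform through an internet browser using a smartphone, tablet, computer, or laptop for patient care purposes".

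**Reach.** Study sites says: "We anticipate that all Network practitioners stratified by state, urban/rural, and practice size, will be eligible to participate". Table 3 repeats this under Network site selection.

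**What is to be learned.** A secondary objective is to "Evaluate practitioner and patient acceptance of FollowApp.Care". Hypothesis 4 expects that performance expectancy, effort expectancy, social influence and behavioral intention "will be consistent with high acceptance of the FollowApp.Care platform". The Background, and again the Discussion, adds: "We will also be able to gauge to what extent practitioners are interested in adopting mHealth technology".

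**Who answers, and when.** Study design invites all participating practitioners to complete a questionnaire. Table 3 says that, once the patient component has concluded, "we will administer the UTAUT Questionnaire to all participating practitioners". Table 2 gives the time as "After practitioner completes enrollment of all their patients" and describes the content as "performance expectancy, effort expectancy, social influence, and facilitating conditions as direct determinants of behavioral intention and behavior".

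**Stated limits.** The Limitation section names confounding and missing data. It does not mention selection of practitioners on willingness.

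**The concern.** Practitioners who do not want the platform are excluded before any acceptance question is asked. The UTAUT then describes only those who remain. A sentence about how far practitioners are interested in adoption will be read as applying to dentists, or at least to Network dentists, but the people needed to answer it are absent by design. Behavioral intention is affected most directly, because intending to use a tool is close in meaning to being willing to use it.

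At stake is the generality of a secondary conclusion. A favourable UTAUT result could be reported as evidence of broad interest among dentists when it shows only that willing users remained favourable. The selection works toward acceptance, and a confidence interval computed from the enrolled dentists would not reveal it.

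**Working it through.** **1. The plan's own figures.** The article states no sample size, power or expected value for practitioner acceptance. Its only sample-size arithmetic concerns patients: 3147 × (1 − 0.40) = 1888.2, stated as 1888. That reproduces, but it plays no part here.

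**2. The passages side by side.**

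| Question | Who would have to be counted | Who is counted |
|---|---|---|
| How far are practitioners interested in adopting? (Background, Discussion) | Willing and unwilling practitioners | Willing only (eligibility criteria) |
| Is acceptance high? (Hypothesis 4) | Not stated | Participating, hence willing, practitioners (Study design, Table 3) |
| How do users rate it after use? (secondary objective) | Users | Users |

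Only the third row matches. The log of screened and enrolled subjects in Table 3 sits under patient screening, and the article describes no count of practitioners who decline.

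**3. What the missing group could do to a proportion.** Let w be the share of practitioners who are willing, a the acceptance among the willing, and u the acceptance among the unwilling. Acceptance among all of them is w·a + (1 − w)·u. The study estimates only a. None of the three is given in the documents, so every input below is an assumption. With a = 0.80 and u anywhere from 0 to 0.80:

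| w | u = 0 | u = 0.20 | u = 0.80 |
|---|---|---|---|
| 0.90 | 0.72 | 0.74 | 0.80 |
| 0.75 | 0.60 | 0.65 | 0.80 |
| 0.50 | 0.40 | 0.50 | 0.80 |

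Every row runs up to no bias at all. For comparison, the sampling half-width at 80% is 1.96 × √(0.8 × 0.2 / n). That is 6.4 points for 150 practitioners and 5.3 points for 215, the recruitment range in the Sample size section. Selection could therefore exceed sampling error, but the documents do not show that it does.

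**4. What it could do to a score such as behavioral intention.** Suppose prior willingness and the later score are jointly normal with correlation ρ, and the top share w is enrolled. Selection then raises the mean by ρ·φ(z)/w standard deviations, where φ is the standard normal density at the cut-off z. For assumed ρ from 0.3 to 0.7:

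- w = 0.90: 0.06 to 0.14 SD
- w = 0.75: 0.13 to 0.30 SD
- w = 0.50: 0.24 to 0.56 SD

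The direction is upward for any positive ρ. The amount cannot be determined from the article.

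**5. Timing of the UTAUT.** Table 2 ties it to the practitioner finishing enrolment of all his or her patients. Table 3 ties it to the end of the patient component and covers all participating practitioners. Under Table 3 a dentist who stops early is still asked. Under Table 2 alone it is unclear when, or whether, that dentist is asked.

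**6. Eligibility wording.** Study sites expects all Network practitioners to be eligible and itself says that the Network includes dental hygienists. The criteria require a dentist, study readiness, a weekly listed procedure and willingness to use the platform. The two statements do not agree, even with willingness set aside.

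**The case against.** The strongest reply is that willingness to open the platform is an operational condition and is not the same as acceptance. Nobody can report on usage, ease of use or workload without using the tool. The article defines practitioner acceptance in those terms and measures it after real use. Hypothesis 4 also covers performance expectancy, effort expectancy and social influence, which willingness at entry does not settle. The pilot described in the Background met workflow, logistical and alert-handling barriers, so willing users may well rate the platform poorly. All of this stands, and it is why the criterion is not at fault.

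A reader might go further and infer that Hypothesis 4 can hardly fail, or that the study says nothing about acceptance. The documents do not support either, for the reasons just given. A reader might also infer that dentists who give up leave no score. Study design and Table 3 address all participating practitioners, so that inference rests on Table 2 alone. Payment after the UTAUT is presented as a retention measure; it encourages response and does not by itself exclude dissatisfied users. Nor does the point extend to a failed patient hypothesis: the metrics in Hypothesis 4 are answered by practitioners, and no hypothesis on patient usability scores is stated.

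It can also be said that the adoption sentence is a general remark rather than an objective, that Study sites is hedged as an anticipation, and that refusal logs belong in recruitment procedures which an article does not reproduce. The last is fair, and absence of a log is not the finding. The remark is nonetheless made twice as something the study will deliver, and the stated entry rule does not allow it.

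**Conclusion.** The point holds as one about the scope of inference. Followed as written, the plan can estimate acceptance after use among dentists willing to try FollowApp.Care. It cannot support the statement that it will gauge the extent of practitioners' interest in adoption. The behavioral intention part of Hypothesis 4 is tilted toward confirmation by an unknown amount; the other constructs are less directly tied to the entry criterion.

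The conclusion rests on the entry criterion and on the UTAUT going only to participants, both of which are explicit. The direction of the tilt assumes that prior willingness and later intention are positively related. The numerical ranges shown are illustrations on assumed inputs and are not estimates of the bias. The primary pain and satisfaction outcomes and the patient sample size are not affected.

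**What to change.** Keep the willingness criterion, and make four changes.

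1. **Count refusals.** Within existing recruitment, have Network coordinators record practitioners who are otherwise eligible and decline, with a reason code for not being willing to use the platform. Report willing / (willing + declined because of the platform) as the measure of interest. This should start early, since refusals are hard to reconstruct later.
2. **Limit the claim.** Word Hypothesis 4 and the adoption sentence in the Background and Discussion as applying to practitioners willing to use the platform. Name this selection in the Limitation section.
3. **Settle the UTAUT timing.** Reconcile Table 2 with Table 3 so that practitioners who stop enrolling early are explicitly included. Add a sensitivity bound in which enrolled practitioners who do not return the UTAUT count as not accepting: with k accepting among r responders of n enrolled, report k/n beside k/r.
4. **Reconcile eligibility.** Bring the sentence in Study sites, and its repeat in Table 3, into line with the practitioner criteria.

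The cost is one extra field in the recruitment log, one clarified trigger for an existing questionnaire, and edits to wording. The acceptance statement becomes narrower and probably less favourable.

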### Study outcome measures

This study has two primary outcomes, which reflect 1) pain experience and 2) patient pain management satisfaction. *Pain experience* refers to both pain intensity and pain interference. *Pain intensity* is an assessment of how much a patient hurts. The response categories range from “No pain” to “Very severe” on a 10-point Likert scale [39]. Pain intensity is a relatively homogeneous dimension, and most measures of pain intensity tend to be interchangeable. It was selected because of its relevance to dental patients and practitioners, applicability to all conditions, including acute postoperative dental pain for assessing symptoms, ease of administration, and the relative accuracy with which most adult patients gauge pain. *Pain interference* refers to the extent to which patients have experienced interferences that have prevented them from activities of daily living (ADL), falling asleep, and staying asleep. The response categories range from “Does not interfere” to “Completely interferes” on a 10-point Likert scale. *Patient pain management satisfaction* refers to the level with which patients are satisfied with the overall pain management following their procedure and shared pain management strategies. The response categories range from “Extremely dissatisfied” to “Extremely satisfied” on a 10-point Likert scale. Additionally, it encompasses whether the patient participated in the decision-making regarding their treatment. The response categories range from “Not at All” to “Very Much So” on a 10-point Likert scale.

Secondary outcomes include 1) *Analgesic medications used by patients* that are reported through FollowApp.Care, frequency and dose prescribed captured through the eCRF completed by the practitioners; adherence to pain medications prescribed collected from the patient-reported data through FollowApp.Care, 2) *Concordance with pain management strategy* as recommended by the practitioner (reported on the eCRF) and reported by the patient. The pain management strategy of each practitioner will be captured on the eCRF, and the mHealth questionnaire will capture the corresponding patient adherence. 3) *Other pain management strategies* used by patients (post-op pain management strategies including usage of other pain management strategies, such as non-medicine methods for pain relief), 4) *Practitioner acceptance* of the platform (usage, perceived usefulness, ease of use, and impact on clinical workload), 5) *Patient perceived usability* with the platform (usefulness and ease of use of the platform), and 6) *Other complications* related to immediate postoperative complications (bleeding and increased swelling).

Other covariates are *Baseline pain intensity, Patient demographic* variables, *Type of procedure* (CDT), P*ractitioner demographic* variables, *Practitioner specialty, Practitioner years in practice (*the year of graduation from dental school), and Practitioner assessment of *expected pain intensity.*

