### Instruments for data collection

Specific instruments include:mHealth questionnaires

The mHealth Questionnaire #1 includes questions about pre-procedural pain and patient demographics. The mHealth Questionnaire #2 includes questions about pain intensity and pain interference. Pain intensity questions are based on the PROMIS Item Bank v.1.0 – Pain Intensity Scale [39]. On days 1, 3, 5, 7, 14, and 21, patients are asked: “What is your level of pain right now?” On day 7, patients are also asked: “How intense was your pain at its worst since the procedure?” *Pain Interference* questions were taken from the validated Oral Health Impact Profile-14 (OHOP-14) [40] and the Revised American Pain Society Patient Outcome Questionnaire (APS-POQ-R) [41–43] questionnaires to focus attention on the small subset of activities (e.g., sleep) common to post-operative dental patients. If, on days 14 and 21, patients answer the pain intensity question (“What is your level of pain right now?”) as positive (> 0), they will also be asked the six pain interference questions. The mHealth Questionnaire #2 will also collect the following additional information: type and frequency of pain-relief medications taken and the presence of concurrent symptoms such as bleeding, visible swelling, suppuration (pus), and/or fever. The mHealth Questionnaire #3 includes questions from the 2nd mHealth questionnaire and questions about patient pain management satisfaction (see Additional file 1: Appendix 1).2.System Usability Scale (SUS) questionnaire

*FollowApp.Care usability as perceived by patients will be measured* by the system usability scale (SUS) [44–46] questionnaire to measure the usefulness and ease of use of the FollowApp.Care platform. The validated SUS is a simple questionnaire that uses a ten-item attitude Likert scale, giving a global view of subjective usability assessments (see Additional file 2: Appendix 2).3.Unified Theory of Acceptance and Use of Technology (UTAUT)

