### Sample size

A minimum of 150 and up to 215 dental providers will be recruited, and each provider will be expected to enroll an average of 21 patients for a total of 3147. Assuming a 40% missing data rate among enrolled patients throughout the duration of the study, there will be 1888 patients remaining. This includes patient non-response rates as well as item non-response rates for the outcome of interest during the study period. Given a sample of 1888, the GLMM model for repeated measures will be able to detect a 20% reduction in pain intensity between procedure groups over time with 80.0% power. The minimum sample size was derived by the “longpower” sample package in the R statistical computing environment.

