### Statistical analysis

Standard descriptive statistics will be used to describe both patient and practitioners’ characteristics using 5 data capture methods: 1) the SUS questionnaire, 2) the mHealth Questionnaire distributed on pre-specified days post procedure, 3) the UTAUT questionnaire, 4) the debriefing/interviews, 5) and the practitioner eCRF. Summary statistics such as means, medians, and ranges will be produced for all measured continuous variables. Frequencies and percent contributions will be computed for all categorical and ordinal variables. Graphical methods like X-charts will examine distributions over time and identify potential, influential time points. The balance of baseline characteristics and measures between groups will be compared using appropriate tests, including chi-squared tests, student t-tests, and Wilcoxon rank-sum tests.

A challenge for this non-randomized study is confounders – pre-existing variables that affect the outcomes and differ between the treatment groups. In order to reduce bias, potential confounders variables will be adjusted in regression models for the analysis. Once participants discontinue the study, they will not be contacted and will not be replaced as the power calculation has accounted for them. If the discontinuation rate is high, the study team PIs will discuss how to proceed with the Network and NIDCR. We will create a missing category for all missing data and assess the need for any imputation methods.

We will estimate the difference in intensity, pain interference, and patient satisfaction dependent on the treatment type. The relative risk (RR) will be the measure of association reported along with 95% confidence intervals. Pain, interference, and satisfaction at the end of the study will be compared among the treatment categories. To model the differential treatment (CDT Grouping) effect on patients’ pain intensity, interference, and satisfaction, on, we will use GLMMs using a Poisson link. Models will include time, treatment type, age, gender, race/ethnicity, medications, and no medication methods as fixed effects. In addition, dentist and Network regions will be included as random effects in the models to account for correlations within clusters.

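### A relative risk is planned for patient satisfaction, a bipolar rating with no true zero, so the reported effect depends on how the answers happen to be coded

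*Protocol article*

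**What the plan says.** All references are to the protocol article.

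- **Study outcome measures** names two primary outcomes: pain experience (intensity and interference) and satisfaction with pain management. Intensity is rated "on a 10-point Likert scale [39]. Pain intensity is a relatively homogeneous dimension", starting at a no-pain anchor. Interference has the same length and starts at an anchor meaning no interference. The satisfaction item "refers to the level with which patients are satisfied with the overall pain management"; its anchors are extreme dissatisfaction and extreme satisfaction. A companion item on taking part in treatment decisions belongs to the same outcome. The section gives verbal anchors but no numeric end points.
- **Instruments for data collection** says that patients who on days 14 and 21 answer the intensity question "as positive (> 0), they will also be asked the six pain interference questions".
- **Statistical analysis** applies generalized linear mixed models with a Poisson link to intensity, interference and satisfaction, with dentist and Network region as random effects. It fixes the effect measure: "The relative risk (RR) will be the measure of association reported along with 95% confidence intervals".
- **Sample size** states its target for intensity only: the model is said to "detect a 20% reduction in pain intensity between procedure groups over time with 80.0% power".

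**The concern.** A Poisson-type model with a log link yields, on exponentiating a coefficient, a ratio of expected scores. Such a ratio can be interpreted when zero means absence of the thing measured: half the pain, a fifth less interference. The satisfaction item passes from strong dissatisfaction through a neutral region to strong satisfaction. Its lowest category is the negative extreme, not an absence of satisfaction, and whether that category is stored as 0 or 1 is a convention. The planned ratio inherits the convention.

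At stake is the reported effect for Hypothesis 3. Two analysts following the plan faithfully, with the same answers but different codings, would publish different effect sizes and intervals for a primary outcome. Neither figure could be set beside the intensity and interference ratios as if all three measured the same kind of relative change.

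**Working it through.** **The plan's own figures.** None is given for satisfaction. The Sample size section concerns intensity. Its attrition step reproduces: 3147 × (1 − 0.40) = 1888.2, stated as 1888. The 80.0% power cannot be recomputed from the article, which gives no mean, SD, correlation or group allocation. This point does not depend on it.

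**Inputs.** From the article: a ten-category satisfaction item, a Poisson-link model and a ratio as effect measure. I read the Poisson link as a log link. Assumed, because the article gives no means: a reference mean m coded from 0 and a comparison mean of 0.8m, so that the ratio coded from 0 is 0.80. Covariates and random effects are left out of the illustration.

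**Formulas.** Coding the same answers one unit higher adds 1 to both means.

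- Ratio coded from 0: 0.8m / m = 0.80
- Ratio coded from 1: (0.8m + 1) / (m + 1)
- Difference under either coding: 0.8m − m = (0.8m + 1) − (m + 1) = −0.2m

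**Results.**

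| m coded from 0 | Ratio from 0 | Ratio from 1 | Mean difference, both codings |
|---|---|---|---|
| 8.0 | 0.80 | 7.4/9.0 = 0.82 | −1.6 |
| 5.0 | 0.80 | 5.0/6.0 = 0.833 | −1.0 |
| 3.0 | 0.80 | 3.4/4.0 = 0.85 | −0.6 |
| 2.0 | 0.80 | 2.6/3.0 = 0.867 | −0.4 |
| 1.0 | 0.80 | 1.8/2.0 = 0.90 | −0.2 |

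The ratio moves with the coding in every row; the difference moves in none. The movement is modest when satisfaction is high and grows as the reference mean falls.

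**Whether intensity and interference share the problem.** The branching rule works only if the no-pain answer is stored as 0, so the origin for intensity is fixed. The lowest interference anchor is a natural zero, and nothing in the article suggests another coding. A ratio can be defended for both, provided that those anchors are coded 0.

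**The case against.** **Is the scale origin contradictory?** A reader might infer a conflict between a ten-point scale and a rule that needs a zero. The documents do not support that. A 0–9 scale has ten points and a zero, so both sections can be true. If ten-point is loose wording for 0–10, the origin is still 0. Only a 1–10 coding would clash, and no section states one.

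**Is the 20% target ambiguous?** A reader might also infer that the design effect depends on where the scale starts. The target is stated for intensity only, and the branching rule puts the intensity origin at 0. The shifts in the table are therefore no criticism of the sample size.

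**Are missing end points a finding?** The article refers the reader to Appendix 1 for the questionnaires. That file is not shown, and a condensed article may leave response codes to it. This objection stands: the missing end points are at most a point of clarity.

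**Would the appendix settle satisfaction too?** It would settle which ratio is computed. It would not turn the lowest satisfaction category into an absence of satisfaction. The ratio is a choice the article makes, not a detail it omits, so this objection does not remove the point.

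**Is the effect small?** At high means, yes: 0.80 against 0.82. That bears on the size of the problem, not on whether the measure is well defined.

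**Conclusion.** The point holds for satisfaction. The plan fixes a ratio for a primary outcome whose scale has no true zero, and the size of that ratio depends on an arbitrary coding choice. Under the assumed means, a ratio of 0.80 coded from 0 becomes 0.82 at a reference mean of 8.0 and 0.90 at 1.0 when the same answers are coded from 1. These figures rest on assumed means, an unadjusted two-group comparison and a log link; the article allows no firmer estimate.

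The decision-participation item runs upward from an anchor of none at all, so the bipolar argument applies to it less directly. It belongs with satisfaction because the article makes it part of the same outcome. No defect is shown in the intensity or interference ratios, the branching rule or the detectable effect.

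**What to change.** In Statistical analysis:

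1. Report satisfaction and decision participation as adjusted mean differences with 95% confidence intervals, from a linear (identity-link) mixed model with the same fixed and random effects. The time term drops out, since Hypothesis 3 and Table 2 place satisfaction at day 7 only.
2. Limit the ratio to intensity and interference, and state that their lowest anchors are coded 0. Any such item stored from 1 has 1 subtracted in the analysis data set.

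As a minor clarification, print the numeric end points in Study outcome measures so that they agree with the > 0 rule in Instruments for data collection. A 0–9 range fits the present text; if the deployed items run 0–10, the ten-point description needs correcting.

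The cost is a change of wording and one changed model, with no extra data. The small downside is that satisfaction is reported on a different effect scale from the other two outcomes.
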